### Outcomes {12}

The primary outcome of the trial is changes in mean systolic blood pressure (SBP) from baseline (T0) to 12 months (T2). The key secondary outcomes are changes in mean diastolic blood pressure (DBP) and changes in biochemical indexes related to hypertension from T0 to T2. The other secondary outcomes include changes in lifestyles, self-management adherence, and hypertension awareness from T0 to T1 (6 months) and T2. In addition, work efficiency of care providers will be assessed at T2 to validate the model from a care provider perspective.

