### Plans for collection, laboratory evaluation, and storage of biological specimens for genetic or molecular analysis in this trial/future use {33}

In this trial, a blood collection and a 24-h urine collection will be carried out in HMC for each participating patient at T0, T1, and T2. The blood and urine samples will be used for laboratory tests to assess the biochemical indexes related to hypertension (see Table 2). The test results will be sent to investigators and all samples will not be stored. Investigators will not have access to personal identifiers.

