## Statistical methods

### Statistical methods for primary and secondary outcomes {20a}

Statistical analysis will be performed using SPSS version 23.0. All statistical tests will be reported as a two-sided significance level of 5%, and the results will be presented with two-sided 95% confidence intervals (CIs). The data will be treated either by parametric or non-parametric analysis based on the tests for normal distribution (Shapiro-Wilk test) and homoscedasticity (Levene’s test). We will first conduct detailed exploratory descriptive analyses to collected data using graphical and numerical summaries. Then, comparisons between and within groups will be performed to identify the effectiveness. For categorical variables, the Pearson chi-square test or Fisher exact test will be used; for continuous variables, the Student *t* test or Mann-Whitney test will be used. In case of significant baseline differences, a linear mixed model will be constructed for the outcomes adjusting the baseline using the following covariates as appropriate: baseline SBP, demographics (age, gender, education levels), and BMI. Only those confounding factors found to be statistically significant to the outcomes by analysis of covariance will be included in the final model.

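### The covariate list for the baseline-adjusting model does not provide for adjusting DBP, the blood indexes and most other secondary outcomes for their own T0 value

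*Protocol article*

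**What the plan says.** All of the following stands in the protocol article.

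- **Default comparison** (Statistical methods {20a}): "for continuous variables, the Student *t* test or Mann-Whitney test will be used", without covariates.
- **When a model is used** (same section): "In case of significant baseline differences, a linear mixed model will be constructed for the outcomes".
- **Covariates of that model** (same section): "a linear mixed model will be constructed for the outcomes adjusting the baseline using the following covariates as appropriate: baseline SBP, demographics" (age, gender, education) and BMI. The list is written once, for the outcomes in the plural, in a section covering primary and secondary outcomes.
- **Screening** (same section): "Only those confounding factors found to be statistically significant to the outcomes by analysis of covariance will be included in the final model".
- **Outcomes** (Outcomes {12}): the primary outcome is the change in SBP from T0 to T2. Then: "The key secondary outcomes are changes in mean diastolic blood pressure (DBP) and changes in biochemical indexes related to hypertension from T0 to T2". Changes in lifestyles, self-management adherence and hypertension awareness are the other secondary outcomes measured on patients.
- **Availability of T0 values**: Implementation {16c} puts body measurement, clinic BP, laboratory tests and questionnaires in the baseline assessment. The specimen section {33} adds that "a blood collection and a 24-h urine collection will be carried out in HMC for each participating patient at T0, T1, and T2".

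**The concern.** The stated purpose of the model is to deal with baseline differences. For SBP and BMI the list contains the variable that would need adjusting. For the rest it does not. If DBP or LDL differs between arms at T0 and triggers the model, the candidates offered are SBP, demographics and BMI, and the variable that differs is not among them.

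This matters because a change from T0 is, in general, negatively correlated with its own T0 value. The arm that happens to start higher tends to fall further with no treatment effect. Subtracting the baseline, as the outcome definitions do, does not remove that. The outcomes affected include all the key secondary ones. Precision available from T0 data that will be collected anyway is also left unused.

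**Working it through.** **1. The plan's own figure.** From Sample size {14}: difference 5 mmHg, SD 16.5 mmHg, two-sided 5%, power 0.80. n per group = 2 × (1.960 + 0.842)² × 16.5² / 5² ≈ 171, as stated. Attrition: 342 / 0.85 = 402.35, against 402 stated, which is a matter of rounding. At 1:1 allocation, 402 / 2 = 201 per arm are compared at baseline. The point below changes none of these figures.

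**2. Outcomes without their own baseline on the list.** From Table 2: DBP (1), blood indexes (10), WHR, IPAQ, urine sodium, urine potassium, HB-MAS, HK-LS (6). Total 1 + 10 + 6 = 17. SBP and BMI are on the list. Work efficiency is assessed at T2 only, and self-monitoring adherence comes from the system log with no evident pre-trial value, so neither is counted.

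**3. Size of a triggering imbalance.** Just significant at two-sided 5% with 201 per arm: 1.96 × √(2/201) = 0.196 SD. Under randomisation each variable has about a 5% chance of such a difference, so the expected number among the 17 is 17 × 0.05 = 0.85.

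**4. Bias given that imbalance.** The documents give no correlations, so two are assumed: rho (T0 with T2 of the outcome) and r (baseline SBP with the outcome's T0 value). Equal variances at T0 and T2 are also assumed, and baseline SBP is taken to relate to the T2 value only through the T0 value.

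- Unadjusted change: (1 − rho) × 0.196. At rho = 0.5: 0.098 SD.
- After adjusting for baseline SBP only: (1 − rho) × 0.196 × (1 − r²). At rho = 0.5: 0.098 × 0.99 = 0.097 SD for r = 0.1, and 0.098 × 0.75 = 0.073 SD for r = 0.5.
- After adjusting for the outcome's own T0 value: about 0.

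**5. Check by simulation.** 171 per arm analysed, no treatment effect, T0 imbalance fixed at 0.196 SD, 3,000 replicates per setting:

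| rho | r | Bias, SBP only (SD) | False positives, SBP only | Bias, own T0 (SD) | False positives, own T0 |
|---|---|---|---|---|---|
| 0.3 | 0 | −0.133 | 13.6% | 0.003 | 5.2% |
| 0.3 | 0.6 | −0.086 | 8.1% | 0.001 | 5.1% |
| 0.5 | 0 | −0.097 | 10.8% | 0.001 | 4.7% |
| 0.5 | 0.6 | −0.064 | 8.3% | −0.002 | 5.7% |
| 0.7 | 0 | −0.057 | 8.7% | 0.002 | 5.4% |
| 0.7 | 0.6 | −0.039 | 6.9% | −0.001 | 4.9% |

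**6. Precision (illustrative).** The change-score variance is 2(1 − rho) in units of the outcome variance. Own-baseline adjustment reduces it to 1 − rho², a factor of (1 + rho)/2: 0.65, 0.75 and 0.85 at rho = 0.3, 0.5 and 0.7. Adjusting for baseline SBP only gives a factor of 1 − r²(1 − rho)/2. At rho = 0.5 this is 0.9975 for r = 0.1 and 0.9375 for r = 0.5, against 0.75 with the own T0 value.

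**The case against.** The best case for the plan has four parts.

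- **The list is flexible.** Covariates are used where suitable and then screened. A reader might infer that baseline SBP sits in every model. The text does not support that: SBP is a candidate and may drop out. This does not help the other outcomes, however, because both provisions only select from the list and cannot add baseline DBP or LDL.
- **The form of the mixed model is not given.** Trial design {8} describes measurements at three time points, so T0 could enter as a response. With a T0 mean common to both arms, each outcome would be adjusted for its own baseline. With separate arm means at T0 and complete data, the group-by-time contrast is just the unadjusted difference in change. The article states neither form. A reader might conclude that these outcomes are never adjusted; what the documents support is that no such adjustment is provided for.
- **Detail belongs in the SAP.** This would answer a silent protocol. Here the article states a list, and an analysis plan that follows it would inherit the gap.
- **Randomisation protects the comparison.** This stands. Averaged over randomisations the change comparison is unbiased, and the figures in steps 4 and 5 apply only when an imbalance of that size has occurred.

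**Conclusion.** The point holds, for secondary outcomes only. The single candidate list omits the own T0 value of 17 outcomes, including all the key secondary ones, and no other section supplies it. SBP's own baseline is already listed, and the sample size is unaffected.

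Given a just-significant imbalance of 0.196 SD, adjusting for baseline SBP alone leaves 0.097 to 0.073 SD of spurious difference at rho = 0.5 and r = 0.1 to 0.5. Over the simulated range (rho 0.3 to 0.7, r 0 to 0.6) the residual is about 0.13 to 0.04 SD, with a false-positive rate of about 14% to 7%, against about 0 and 5% with own-baseline adjustment. All of this rests on assumed correlations.

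A reader might also apply the SBP design to these outcomes and report a power gain, for example from 79.8% to 89.7% at rho = 0.5. The documents do not support that as a finding. The effect of 5/16.5 is specified for SBP, no power is stated for any secondary outcome, and the comparison is with the unadjusted t test. The gain would therefore depend on running the adjusted model routinely, which is a separate question. Only the variance factors in step 6 can be offered, as illustration.

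**What to change.** In Statistical methods {20a}, name the T0 value of the outcome being analysed as a prespecified covariate in the model for each continuous outcome that has one, and exempt it from the significance screen. Without that exemption the screening sentence could remove it again. Baseline SBP may stay as an additional covariate. System-log outcomes without a T0 value are left out of the rule.

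The T0 values are already scheduled, so there are no new data, visits or patients. Each model spends one degree of freedom. For skewed outcomes, such as some laboratory values or questionnaire scores may prove to be, the plain Mann-Whitney test takes no covariate, so a transformation or a rank-based analysis of covariance has to be chosen in advance in its place.

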### Interim analyses {21b}

This is not applicable. No formal interim analysis of the primary and secondary outcomes is planned.

### Methods for additional analyses (e.g., subgroup analyses) {20b}

We will also perform subgroup analyses of the primary and secondary outcomes stratified by following variates at the initial management (1 week after baseline): BMI (< 24, ≥ 24), management level (level 1 and level 2), and self-management adherence.

### Methods in analysis to handle protocol non-adherence and any statistical methods to handle missing data {20c}

The statistical analysis will be conducted on an intention-to-treat (ITT) basis. For incomplete assessments (missing data), multiple imputation will be applied using both an optimistic and pessimistic scenario.

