### Sample size {14}

The power calculation is based on the primary outcome measure and aims for a mean systolic blood pressure variation of 5 mmHg with a standard deviation of 16.5 mmHg (the effect size is based on a previous study [29]). Assuming an α of 5%, and power of 0.80, 171 patients per group are required at the end of the trial (342 in total). Considering an attrition percentage of 15%, our aim is to include a minimum of 402 patients at baseline.

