### Plans to promote participant retention and complete follow-up {18b}

At each assessment point (T1 and T2), all patients will receive a phone call from CMs to remind them of the upcoming data collection and free offline consultation with doctors if they attend the assessment. Patients who prematurely discontinue from the study before the 6-month evaluation and do not attend any assessment will have the following evaluations performed, if possible: First, GPs will call them to invite them to insist on the trial or attend the assessment; if refused, a brief interview will be conducted to investigate the reasons for discontinuation. Second, the system log data of these patients will be fully explored to extract useful information.

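### Missing SBP data are to be imputed only under an optimistic and a pessimistic scenario, with no neutral principal analysis and no rule on which result decides; the extra steps to recover dropouts end at month 6 although the endpoint is at month 12

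*Protocol article*

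**What the plan says.** The missing-data section (item 20c) has two sentences. The first sets the analysis population: "The statistical analysis will be conducted on an intention-to-treat (ITT) basis". The second is the whole method for missing values: "For incomplete assessments (missing data), multiple imputation will be applied using both an optimistic and pessimistic scenario". Neither scenario is defined, and neither is named as the principal result.

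For the comparison itself, the statistical methods section (item 20a) states that "for continuous variables, the Student *t* test or Mann-Whitney test will be used". It adds a model under one condition: "In case of significant baseline differences, a linear mixed model will be constructed for the outcomes adjusting the baseline".

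The primary outcome (item 12) is the change in SBP from baseline (T0) to 12 months (T2), and SBP is also measured at 6 months (T1). The sample size section (item 14) plans for losses: "Considering an attrition percentage of 15%, our aim is to include a minimum of 402 patients at baseline".

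On retention (item 18b), every patient gets a reminder call before both T1 and T2, with the offer of a free consultation for attending. Further steps are a GP call inviting the patient to return or be assessed, an interview on reasons if the patient refuses, and a search of the system log. These are set for a narrower group: "Patients who prematurely discontinue from the study before the 6-month evaluation and do not attend any assessment will have the following evaluations performed".

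**The concern.** An optimistic and a pessimistic imputation are, by their names, directional. Each pushes the missing values one way, and neither is meant as the best estimate of the treatment effect. Such scenarios are useful around a principal analysis, but here none is named. An analyst who follows the text obtains two ITT results and no rule for choosing between them. If they fall on opposite sides of the significance threshold, the reading of the trial is settled after the data are seen.

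The trial's own discussion makes this more than a formality. It warns that poor acceptance of the system would raise attrition, and that patients in the open-label control group may leave. Loss that differs by arm is therefore a foreseen risk.

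The retention rule bears on the same problem. A patient who attends T1 and leaves at month 8 lacks exactly the measurement that the primary outcome needs, yet falls outside the extra recovery steps. So does one who stops at month 4 but still comes to T1.

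**Working it through.** **Inputs.** Difference 5 mmHg, SD 16.5 mmHg, two-sided alpha 5%, power 0.80, 171 completers per group, 15% attrition, 402 at baseline (items 14 and 20a). The scenario shifts are not in the documents and are assumed below.

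**1. The plan's own figure.** n per group = 2 × (1.96 + 0.842)² × 16.5² / 5² ≈ 171. Then 342 / 0.85 = 402.35, against 402 stated. The sample size reproduces.

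**2. Precision.** SE = 16.5 × √(2/171) = 1.784 mmHg. The smallest significant difference is 1.96 × 1.784 ≈ 3.50 mmHg. An observed 5 mmHg gives z = 5 / 1.784 = 2.80, p = 0.005.

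**3. Effect of a scenario.** With 15% missing per arm (about 30 of 201), moving the imputed mean by s mmHg in one arm moves the difference by 0.15 × s. Moving both arms in opposite directions moves it by 0.30 × s. The completers' SE is kept as an approximation.

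| Assumed shift s | Arms shifted | Pessimistic, mmHg (p) | Optimistic, mmHg (p) |
|---|---|---|---|
| 5 mmHg | one | 4.25 (0.017) | 5.75 (0.001) |
| 5 mmHg | both, opposite | 3.50 (0.0498) | 6.50 (0.0003) |
| 8.25 mmHg (0.5 SD) | one | 3.76 (0.035) | 6.24 (0.0005) |
| 8.25 mmHg (0.5 SD) | both, opposite | 2.525 (0.16) | 7.475 (<0.001) |
| 16.5 mmHg (1 SD) | one | 2.525 (0.16) | 7.475 (<0.001) |
| 16.5 mmHg (1 SD) | both, opposite | 0.05 (0.98) | 9.95 (<0.001) |

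**4. Tipping point.** The pessimistic result loses significance once the difference falls by more than 5 − 3.50 = 1.50 mmHg. That needs a shift above about 1.50 / 0.30 = 5 mmHg with both arms moved, or about 1.50 / 0.15 = 10 mmHg with one arm moved. The 5 mmHg row for both arms therefore sits on the boundary.

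**5. The other direction.** An observed 2.5 mmHg (z = 2.5 / 1.784 = 1.40, not significant) becomes 2.5 + 2.475 = 4.975 mmHg (z = 2.79) under an optimistic 0.5 SD shift in both arms.

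**6. Does another section supply the neutral analysis?** No. The t test and the Mann-Whitney test do not deal with missing values. The mixed model could, if fitted to T0, T1 and T2, but it is called for only when baseline differences are significant, and its stated purpose is covariate adjustment.

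**The case against.** The best defence is that the sentence does not say the two scenarios are the only analyses and calls neither of them primary. Running both is a recognised way to bound an estimate, and the authors may have meant exactly that. This is also a journal article with a short missing-data section. The imputation model, the shifts and the ranking of analyses are details that a statistical analysis plan commonly holds. That stands as far as the undefined shifts are concerned: their absence alone would be no finding. It does not dispose of the point, because the text does more than stay silent. It ties the imputation to two directional scenarios and offers no principal analysis for them to bound.

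A reader might infer that the trial has two opposed primary results. The documents do not support that: no result is designated as primary, and the two scenarios may agree.

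A reader might also infer that patients lost after month 6 are not pursued at all. That is wrong too. Everyone gets the T2 reminder and the consultation offer, and the discussion adds patient rewards, system guidance and training. Only the further recovery steps are restricted.

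On size, a 1 SD shift is 16.5 / 5 = 3.3 times the planned effect, applied in opposite directions to all missing patients. It is an extreme case and should not be taken as the expected one.

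**Conclusion.** The point holds in this form: the plan names only optimistic and pessimistic imputation, has no standing neutral analysis, and does not say which result decides superiority. Under the planning figures and an observed 5 mmHg, both scenarios remain significant for opposite shifts up to about 5 mmHg, or up to about 10 mmHg in one arm. Beyond that they part. The choice of scenario can therefore decide the conclusion but need not. This rests on assumed shifts, on 15% missing in each arm, and on the completers' SE.

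The retention gap is real but narrower than it may first look: the extra recovery steps leave out anyone who stops between months 6 and 12, and anyone who stops earlier but attended an assessment.

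**What to change.** - Name one principal analysis before results are known: multiple imputation under missing-at-random, done by arm, using baseline and T1 SBP; or a mixed model on T0, T1 and T2 that does not depend on a baseline test. State that this result decides superiority.
- Treat home BP readings only as an optional auxiliary variable. The protocol reserves them for daily management, and control patients receive no management plans, so the amount of home data may differ by arm.
- Keep the optimistic and pessimistic scenarios as labelled sensitivity analyses, with the shift and the arms it applies to stated in advance. A tipping-point range such as the one above would serve.
- Extend the extra recovery steps to anyone who discontinues at any time before T2, and seek the T2 clinic BP.

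Cost: a few sentences in the protocol or analysis plan, some programming and some extra phone calls. The sample size is unaffected.

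### The choice between t and Mann-Whitney by assumption test does not fit multiply imputed data as stated; fix one poolable between-arm estimate in advance

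*Protocol article*

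**What the plan says.** Two sections of the protocol article bear on this.

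- **Statistical methods for primary and secondary outcomes {20a}.** The rule for choosing a method is: "The data will be treated either by parametric or non-parametric analysis based on the tests for normal distribution (Shapiro-Wilk test) and homoscedasticity (Levene’s test". The two candidates follow: "for continuous variables, the Student *t* test or Mann-Whitney test will be used". On reporting: "the results will be presented with two-sided 95% confidence intervals (CIs". A model-based analysis appears only under a condition: "In case of significant baseline differences, a linear mixed model will be constructed for the outcomes adjusting the baseline".
- **Methods in analysis to handle protocol non-adherence and missing data {20c}.** "The statistical analysis will be conducted on an intention-to-treat (ITT) basis", and then: "For incomplete assessments (missing data), multiple imputation will be applied using both an optimistic and pessimistic scenario".

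The primary outcome is the change in SBP from baseline to 12 months (Outcomes {12}), so it falls under both sections. Sample size {14} plans for 15% attrition from 402 patients. The article does not say whether the assumption tests are run on observed or on imputed data, and it names no effect measure for the rank route.

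**The concern.** The choice rule in {20a} presumes a single dataset per outcome: run the assumption tests, read off the answer, apply the matching test. Multiple imputation in {20c} produces several completed datasets per outcome, which may not give the same answer. A t test estimates a mean difference and Mann-Whitney addresses a rank comparison, so a mixture of the two cannot be averaged into one result.

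Pooling by Rubin's rules also needs an estimate and a standard error from each completed set. The t test supplies both. Mann-Whitney, as named, supplies U and a p-value.

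With 15% attrition, about 0.15 × 402 = 60 patients would have an imputed 12-month SBP. An analyst would have to settle, with the outcome data in view, where the rule is run and what is pooled. That is the discretion that prespecification is meant to remove.

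**Working it through.** **The plan's own figure.** From Sample size {14}: difference 5 mmHg, SD 16.5 mmHg, two-sided α 5%, power 0.80.

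n per arm = 2 × (1.960 + 0.842)² × 16.5² / 5² = 2 × 7.85 × 10.89 ≈ 171, as stated (171.9 by the t-based formula). Enrolment: 342 / 0.85 = 402.35, against 402 stated. The sample size reproduces, and the point does not depend on it.

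**Why imputed sets can disagree.** The rule needs three tests to pass: Shapiro-Wilk in each arm, and Levene. At 5% each, treated as independent, a perfectly normal dataset fails at least one with probability 1 − 0.95³ = 14%. A trial near a threshold can therefore pass in one completed set and fail in the next.

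**Simulation.** From the article: SD 16.5, 402/2 = 201 per arm, 15% missing, true difference 0 or 5 mmHg. Assumed, because the article does not give them: data missing completely at random, normal-model imputation within arm, 5 or 20 imputations, assumption tests at 5%, and the shapes below. There were 400 trials per scenario. Ranges span the two true differences.

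| Distribution of change | Sets disagree, 5 imputations | Sets disagree, 20 imputations | All 20 call for t | All 20 call for Mann-Whitney |
|---|---|---|---|---|
| Normal | 26.5-32.0% | 50.3-50.8% | 46.8-47.0% | 2.3-3.0% |
| t, 8 df | 26.0-26.3% | 42.8-43.3% | 8.5-8.8% | 48.3-48.5% |
| Skewness 0.5 | 28.8-29.0% | 47.5-49.0% | 1.0-3.0% | 49.5-50.0% |
| Skewness 1 | 0.0% | 0.3% | 0.0% | 99.8% |

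The Monte Carlo standard error near 50% is √(0.5 × 0.5 / 400) = 2.5 points.

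**Can each route be pooled?** In every simulated trial two estimates were pooled by Rubin's rules (total variance = mean within-set variance + (1 + 1/m) × between-set variance):

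- Mean difference: type I error 4.0-6.3%, power 78-80% at 5 mmHg.
- Mann-Whitney effect P(Y>X) with a placement-based variance: type I error 4.5-5.8%, power 78-82%.

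The Monte Carlo standard error is about 1.1 points for type I error and 2 points for power. Either estimate works if it is fixed in advance. The two verdicts at 5% differed in 1.8-3.3% of trials with no true difference and in 3.5-8.0% at 5 mmHg.

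**The case against.** The strongest reply has four parts.

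1. **Mann-Whitney can be pooled.** A reader might infer that rank results cannot be combined over imputed sets at all, so that the promised CI does not exist on that route. This is not so: P(Y>X) has an estimate and a variance, and it pooled with acceptable type I error. What stands is narrower. U and the p-value do not pool directly, and the article names no rank effect that would.
2. **Re-choosing the test in each set is not stated.** A reader might also infer that the plan will often yield no single p-value. The article neither states nor excludes testing within each completed set. A single choice on observed data is a natural reading, and disagreement between sets is then zero by construction. The percentages above are therefore conditional. What stands is that the primary test is still chosen from outcome data, between two analyses whose verdicts differ in up to 8.0% of the simulated trials.
3. **Details belong in the SAP.** The number of imputations and the pooling rule can wait for an SAP, and their absence here is no fault. The choice by assumption test, however, is stated in this article. An SAP could not fix one poolable analysis without departing from {20a}.
4. **Much of the plan pools normally.** The t test and the linear mixed model do. This is accepted, but the mixed model is used only if a baseline difference is significant, so it does not settle the primary analysis in advance.

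**Conclusion.** The concern holds in a limited form. The stated rule for choosing the test does not fit multiply imputed data, and each way of applying it has a cost. Within each completed set, the sets disagree in about 26-32% of trials with 5 imputations and 43-51% with 20, for normal or mildly non-normal changes, and in 0.0-0.3% at skewness 1. Once on observed data, they never disagree, but the choice remains data-driven.

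These figures rest on the assumed missingness mechanism, imputation model, numbers of imputations and shapes. They show that the problem is realistic under the first reading; they do not predict how often it will occur in this trial.

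The point covers continuous outcomes assessed at 12 months and subject to attrition, with the primary SBP outcome first. It does not cover the measures of provider work efficiency, which come from the system log. It should be corrected before analysis, but it does not undermine the design or the sample size.

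**What to change.** Amend {20a} and {20c} together:

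- Remove the choice by Shapiro-Wilk and Levene for the between-arm comparison of continuous outcomes.
- For each imputed continuous outcome, prespecify one between-arm estimate. For SBP, use a linear model on the change or on 12-month SBP, preferably adjusted for baseline SBP. Fit it in every completed set and pool by Rubin's rules with a 95% CI.
- Log-transform outcomes known in advance to be skewed, such as triglycerides or physical activity scores, and name them beforehand.
- Keep any rank test as a supportive complete-case analysis.

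This always gives one estimate, CI and p-value per imputation scenario. In the simulation the unadjusted pooled mean difference kept power at 78-80%, close to the planned 0.80.

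The cost is a wording change and less analysis work. The downside is that rank tests become supportive only. In the simulation that gave up about 3 points of power in the heavy-tailed and clearly skewed cases (78% against 81-82%), and nothing with normal or mildly skewed changes.
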